**Figure 2 figure2:**
[figure not shown]
Map of EMERALD (Enabling Mobilization, Empowerment, Risk Reduction, and Lasting Dignity) intervention and control areas. Red star=SPARC (Sex Workers Promoting Action, Risk Reduction, and Community Mobilization) center, blue=water, pink=intervention area, and green=control area.

SPARC’s day-to-day operations are bolstered by key collaborations with community providers who offer services at SPARC, enabling these organizations to reach a population they otherwise do not easily access. The Baltimore City Health Department funds 2 nurse practitioners and a medical assistant to run a weekly reproductive health clinic (eg, long-acting reversible contraceptives, Papanicolaou testing, and intrauterine devices) and a twice-weekly sexual health clinic (eg, pre-exposure prophylaxis, HIV and Hepatitis C testing and treatment referrals, and STI testing and treatment). The Behavioral Health Leadership Initiative funds 2 providers to staff a weekly low-threshold medication-assisted treatment clinic at SPARC. Biweekly law clinics are offered through the Legal Aid of Maryland and the Maryland Volunteer Lawyers Network.

SPARC’s reach is expanded through an intensive mobile outreach program, which brings many tangible harm reduction tools and microcounseling to women while they are working and living on the street. The outreach program is deployed throughout south and southwest Baltimore at night and during the day between 3 and 4 times a week, serving 15 to 40 people per shift. Outreach staff work in teams to provide relevant harm reduction education and supplies from the window of the outreach vehicle, through drop-off supply bags, and during community events.

All SPARC and outreach staff receive extensive training as a part of onboarding and continuing education. Training sessions are conducted by the study staff as well as external experts and cover topics such as trauma-informed care, harm reduction principles and practice, interpersonal and systemic violence, safer drug use (eg, safer injection), naloxone administration, gender and sexual identity, and de-escalation and staff safety practices. Understanding that trauma often serves as a direct barrier to care, much of the continuing education at SPARC centers around trauma-informed care and supporting the complex needs of vulnerable individuals.

To ensure equal treatment of all guests, the SPARC center and outreach staff are blind to EMERALD study participation. Limited guest information is collected at intake, primarily their name and birthdate, sex work and drug use history, and service needs. This information allows the team to track service utilization among all women to inform programming and determine whether the intervention is reaching the target population. SPARC guests are asked to sign a consent form indicating that they agree to allow the research team to access their SPARC data. Unique identifiers will be linked between EMERALD and SPARC to determine the frequency of SPARC center interactions among EMERALD participants at the conclusion of all EMERALD data collection. Owing to the quick pace and casual nature of outreach, no identifying information is collected on outreach shifts.

The SPARC program contributes to the innovation of a service model that incorporates health, social, legal, and basic needs (eg, emergency food, shower, laundry, and space to relax) services in a convenient space, paired with a comprehensive outreach program that brings services, supplies, and information to the community, increasing the likelihood of engagement in care and continued service utilization.

### The EMERALD Study

#### Study Design

The primary component of the EMERALD study, which evaluates the SPARC center and associated outreach, is a prospective 2-group comparative nonrandomized trial. Participants were recruited into the control and intervention arms. The intervention area is the south and southwest portion of Baltimore City because of high concentrations of street-based FSWs and a dearth of tailored FSW services, indicated by pink shading (Figure 2). The control group participants were recruited primarily from the southeast and northwest Baltimore. The SPARC center is located within the intervention area, and outreach is conducted in areas with potential sex work activity throughout the intervention area.

The study diagram (Figure 3) illustrates participant progress through the study stages, sample size, and follow-up schedule. Participants completed a survey, HIV testing, and STI testing for chlamydia and gonorrhea during study visits at baseline and at 6, 12, and 18 months. In-depth interviews began at the conclusion of the EMERALD cohort and are currently being conducted with intervention area participants, SPARC staff, and outreach workers. In addition, 100 cross-sectional surveys are being collected in the intervention area to assess program reach in the community beyond the EMERALD cohort.

**Figure 3 figure3:**
[figure not shown]
EMERALD (Enabling Mobilization, Empowerment, Risk Reduction, and Lasting Dignity) study flow. STI: sexually transmitted infection; VDT: venue-date-time.

#### Cohort Study Target Population and Sample

Cohort participants were FSWs aged ≥18 years who live in Baltimore City; self-reported that they had traded sex for money, goods, or drugs 3 or more times in the past 3 months; and were not currently enrolled in our previous cohort study, the SAPPHIRE study [40]. Although transgender female sex workers (TFSWs) who reported being assigned male at birth were encouraged to visit the SPARC center and engage with peer outreach workers, they were excluded from the EMERALD study cohort because of a lack of comparable recruitment locations between the intervention and control areas.

Participants were assigned to a study arm based on the geographic location in which they were recruited. The initial target sample size was 350 women based on power calculations to observe a change in the intervention compared with the control group over the 3 follow-up visits. The assumptions used for the calculation were (1) n=200 in the intervention group and n=150 in the comparison group, (2) lost-to-follow-up (LTFU) rate of 10% to 20% in the intervention (effective n=160-180) and LTFU of 20% to 25% in the comparison group (effective n of 120-112), (3) intraperson correlation (Rho)=0.2-0.4, (4) varying levels of baseline risk behavior rate, and (5) a 2-sided α=.05. Thus, assuming effective sample sizes of n=160 in the intervention and n=112 in the comparison groups, the power is 83% to detect an odds ratio of 0.50, assuming a 20% prevalence rate of a risk behavior (eg, drug use) in the control group and an intraperson correlation of Rho=0.2. For the cumulative incidence outcome, with an average N contributing to the analysis of 170 in the intervention and 120 in the control groups, and assuming annual incidence rate of 6%, the power is 80% to detect a rate ratio of 0.28.

The enrollment target was increased to 450 midway through data collection after power calculations were reassessed based on actual retention rates within the sample, which were closer to 65%. The LTFU rate was higher than anticipated based on previous studies [41], likely because of high incarceration rates, the mobility of the population, and the length of time between study visits (6 months). Although we aimed for a sample of 450 participants, recruitment was stopped at 385 because of reaching saturation in the recruitment areas and repeatedly encountering participants attempting to reenroll in the study.

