#### Cohort Recruitment

EMERALD recruitment began 2 months before the opening of the SPARC center and took place from September 2017 to January 2019. The recruitment strategy for the EMERALD cohort was informed by SAPPHIRE, an earlier prospective cohort study of FSWs in Baltimore, conducted by this study team, which used targeted sampling [50]. Given that recruitment for SAPPHIRE concluded approximately 9 months before the launch of the EMERALD study, we conducted a series of geospatial analyses of possible sex work activity indicators using publicly available data [51] (eg, prostitution charge data and 911 call center reports of suspected prostitution) to understand possible shifts in the geotemporal distribution of sex work throughout Baltimore City (as compared with where we previously recruited FSWs in SAPPHIRE).

In total, the sampling frame for EMERALD consisted of 10 small geographic areas with high concentrations of sex work activity. Among them, 6 were located in the intervention area and 4 in the control area. Compared with our previous targeted sampling recruitment strategy among FSWs in Baltimore City [50], the time and day components of the sampling frame were selected based on analyses of time signatures associated with relevant secondary data in each location with high concentrations of sex work activity and supplemented with additional insights gleaned from SAPPHIRE. Before launching recruitment, staff conducted windshield tours in each location to confirm the presence of sex work activity.

A recreational vehicle (RV) retrofitted with 2 private interview areas and a bathroom for sample collection was driven to the field locations in the intervention and control areas 3 to 5 days per week depending on the interview volume. Each shift lasted approximately 4 hours at the recruitment site and was staffed by 1 field supervisor and 2 interviewers. A community advisory board made up of current and former sex workers provided input on all data collection strategies and instruments.

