### Statistical Analysis

The principal analytic approach will center on generalized linear models for the individual data, with variance components that reflect the potential correlations among FSWs recruited from the same area and between repeated measurements from the same individual at baseline and follow-up visits [55,56]. The main covariate of interest is the intervention indicator. To address aim 1, we consider illicit drug use and irregular condom use as the primary behavioral endpoints.

The effect of the intervention will be assessed with a random effect hierarchical logistic model, with the intervention indicator, time, and their interaction as the main explanatory variables. To adjust for possible imbalances between the 2 areas, we will adjust for baseline confounding factors, including age, length of sex work, and number of sexual partners. The intervention effect will be assessed by comparing time trends in the intervention group with the time trend in the comparison group, as captured by the interaction term. The model will be expanded to include additional demographic covariates and time-dependent indicators of events such as arrest, homelessness, use of health services, or exposure to other prevention activities that are unrelated to the study. Aim 1 also seeks to evaluate the association between the degree of exposure to the intervention and observed behavioral changes. We will explore models that include as covariates participation or exposure to specific intervention components (ie, receiving medical care, drug treatment referral, and legal aid). On the basis of the literature, an 18-month follow-up should be sufficient to document meaningful changes in study outcomes, given the extent of the intervention [57].

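### Arm is fixed by 10 recruitment areas (6 vs 4) and the models include area effects, but the stated power lists only within-person correlation; restate it for the contrasts actually tested

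*Protocol article*

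**What the plan says.** **Allocation.** The protocol article, under Cohort Study Target Population and Sample, states: "Participants were assigned to a study arm based on the geographic location in which they were recruited". Under Cohort Recruitment, "the sampling frame for EMERALD consisted of 10 small geographic areas with high concentrations of sex work activity", of which "6 were located in the intervention area and 4 in the control area".

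**Power.** The Target Population section lists five assumptions: group sizes, loss to follow-up, "intraperson correlation (Rho)=0.2-0.4", varying baseline risk rates, and "a 2-sided α=.05". It then gives two results.

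- Behavioral: "assuming effective sample sizes of n=160 in the intervention and n=112 in the comparison groups", control prevalence 20%, rho 0.2, power 83% for an odds ratio of 0.50.
- Incidence: 170 and 120 women on average, 6% per year, power 80% for a rate ratio of 0.28.

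The later increase of the target to 450 is explained by retention alone.

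**Analysis.** Statistical Analysis plans generalized linear models with "variance components that reflect the potential correlations among FSWs recruited from the same area" and between repeated measurements on one woman. The behavioral effect is read from the interaction of arm and time. Cumulative incidence is first compared in a random-effect logistic model with arm as the only explanatory variable, allowing for nesting in recruitment areas. The same section says that full analysis and power details are available on request.

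**The concern.** Every woman recruited in an area belongs to the same arm. Variation between areas is therefore part of the error of any between-arm comparison, and only 10 areas are available to estimate it. The plan accepts this in its models but not in the published power, where women count as independent once within-person correlation is allowed for. With about 27 to 30 women per area, a small area correlation costs a good deal. The stated power may then promise more than the design can deliver, and a null result could be over-interpreted.

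**Working it through.** **1. Inputs from the article.** n = 160 and 112; control prevalence p1 = 0.20; odds ratio 0.50; rho = 0.2; 3 follow-up visits; two-sided 0.05; k = 6 and 4 areas. The intervention odds are 0.5 × 0.25 = 0.125, so p2 = 0.125/1.125 = 0.111. The area ICC is not given. I assume 0 to 0.05 and areas of equal size.

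**2. Reproducing the 83%.** The mean of 3 visits has variance factor (1 + 2 × 0.2)/3 = 0.467.

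- Difference in proportions: SE² = 0.467 × (0.0988/160 + 0.16/112) = 0.000288 + 0.000667, so SE = 0.0309. Then z = 0.0889/0.0309 = 2.88, and power = Φ(2.88 − 1.96) = 82.0%.
- Log-odds scale: SE = 0.2357, z = 0.693/0.2357 = 2.94, power 83.7%.

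The stated figure is matched with no area term and a normal critical value.

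**3. Adding area variance to that contrast.** Per arm, variance = p(1−p)[ICC/k + (rho − ICC)/n + (1 − rho)/(3n)]. The last column uses noncentral t with 10 − 2 = 8 df (critical value 2.306).

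| Assumed area ICC | SE | z | Power, normal | Power, t on 8 df |
|---|---|---|---|---|
| 0 | 0.0309 | 2.88 | 82% | 71% |
| 0.01 | 0.0387 | 2.30 | 63% | 52% |
| 0.02 | 0.0452 | 1.97 | 50% | 41% |
| 0.05 | 0.0606 | 1.47 | 31% | 25% |

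The log-odds version gives 65%, 52% and 33% (normal) and 54%, 43% and 26% (8 df) at the three positive ICCs.

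**4. The contrast the plan tests.** Step 3 concerns the average level over follow-up. The behavioral test compares time trends. A stable area effect is present at baseline and at follow-up, so it largely drops out of a change. What remains is variation between areas in their trends, and the article gives no figure for it. As a rough guide to the contrast itself, baseline versus mean follow-up has variance factor (1 − rho)(1 + 1/3) = 1.067 instead of 0.467. At rho = 0.2 and no area variation, z falls to about 1.90-1.94 and power to about 48-50%.

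**5. Cumulative incidence.** Here arm is the only term in the first model, so area variance enters directly. Average area size is (170 + 120)/10 = 29. The design effect 1 + 28 × ICC is 1.28, 1.56 and 2.40 at ICC 0.01, 0.02 and 0.05.

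The 80% does not reproduce with 6% as the control rate. Over 1.5 years the expected events are 0.06 × 1.5 × 120 = 10.8 and 0.06 × 0.28 × 1.5 × 170 = 4.28. The SE of the log rate ratio is √(1/10.8 + 1/4.28) = 0.571, z = 1.273/0.571 = 2.23, power 61%. Over 1 year it is 44%. A figure near 80% appears if 6% is the overall rate over 1.5 years: control rate 0.06 × 290/(120 + 0.28 × 170) = 10.4% per year, rate-difference power 81%, with area ICC 0. On that reading, using each arm's own area size (170/6 and 120/4), ICC 0.01 gives 71% (60% on 8 df) and ICC 0.05 gives 45% (36%).

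**The case against.** **The trend test removes level differences between areas.** This stands for the behavioral endpoints. The 63%, 50% and 31% describe an averaged follow-up contrast and must not be read as the power of the planned interaction test. Step 4 also shows that the choice of contrast alone accounts for a large gap from 83%, before any clustering.

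**The analysis already models area.** This also stands. A reader might infer that the intervals will be too narrow and the tests anticonservative. The documents do not support that: the article names neither the reference distribution nor the full random-effect structure, and both are commonly left to an analysis plan. The inference holds only if default large-sample tests without an area-by-time term are used. In that case:

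- A normal critical value where 8 df apply gives a type I error of up to 8.6%.
- Unmodelled area-by-visit variation of 1% or 2% of the variance (assumed values) gives about 9% or 13%. This compares 1.067(1/160 + 1/112) = 0.0162 with the same plus c × (4/3)(1/6 + 1/4), which is 0.0056 or 0.0111.

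**The ICC is unknown.** True. Baseline behavior is similar between arms (heroin 79.5% vs 81.4%, condomless sex with clients 43.8% vs 47.2%). Two arm averages say little about spread among 10 areas, however.

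**Fuller power details exist on request, and enrollment is closed.** Unpublished details could differ, but the published 83% needs no area term. Restated power changes no recruitment decision, though it does affect how the results are read.

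**Conclusion.** The point holds as an inconsistency between the design and models on one side and the published power on the other. The 83% is matched at 82-84% with area ICC 0 and a normal critical value, and no area term is listed for the 80%.

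The size of the loss depends on assumed ICCs. For an averaged follow-up contrast, power is 63% at ICC 0.01 and 31% at 0.05 (52% and 25% on 8 df). For the arm-by-time test the loss cannot be stated, because area-by-time variation is not given, and 8 df apply fully only if that variation is modelled or the analysis is at area level. The objection is most direct for cumulative incidence: design effect 1.28 to 2.40 and about 8 df.

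That the 80% fails to reproduce with a 6% control rate is a separate problem and does not by itself show that clustering was ignored.

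**What to change.** - **Power.** Restate both figures, or the effects detectable at the stated power, for the contrasts actually tested: the arm-by-time interaction for behavior and the arm comparison for cumulative incidence. Give them over a stated range of area ICC (for example 0.01 to 0.05) or area-by-time variance, with small-cluster degrees of freedom, and say that these values are assumed.
- **Analysis.** Allow for area-by-time variation in the trend model. For the primary endpoints, refer arm and arm-by-time effects to t on about areas minus 2 = 8 df, or use an area-level analysis of change. If the full analysis plan already does this, a sentence saying so is enough.

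The cost is plan wording and recomputed figures. Stated power will be lower and intervals wider. No new data are needed.

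### The stated 83% power belongs to an arm comparison averaged over the follow-up visits, not to the group-by-time interaction that the plan uses to assess the effect

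*Protocol article*

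**What the plan says.** In the protocol article, Cohort Study Target Population and Sample, the behavioural power calculation uses "a 2-sided α=.05" and is worked out "assuming effective sample sizes of n=160 in the intervention and n=112 in the comparison groups". It concludes that "the power is 83% to detect an odds ratio of 0.50, assuming a 20% prevalence rate of a risk behavior" in the control group, with "an intraperson correlation of Rho=0.2". The list of assumptions in the same paragraph gives the wider range "intraperson correlation (Rho)=0.2-0.4". The paragraph describes the aim as seeing a change relative to control across the three follow-up visits. It gives no baseline variance, no shape of change over time and no interaction effect size.

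The section Statistical Analysis fits a random-effects logistic model with arm, time and their interaction to the baseline and follow-up measurements. It then says: "The intervention effect will be assessed by comparing time trends in the intervention group with the time trend in the comparison group", with the interaction term as the measure. The primary behavioural endpoints are illicit drug use and irregular condom use.

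On the achieved sample, the article reports "actual retention rates within the sample, which were closer to 65" percent, a target raised to 450, and that "recruitment was stopped at 385 because of reaching saturation in the recruitment areas" (224 intervention, 161 control). It prints no updated power figure.

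**The concern.** A difference in change from baseline is a different quantity from a difference between arms during follow-up. It carries the sampling error of the baseline visit as well, and a linear slope also spreads the information over the shape of the trend. A calculation that uses only follow-up visits will therefore usually show more power than the interaction test has.

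If the printed 83% is taken as the power of the named test, a non-significant interaction may be read as firmer evidence against the SPARC intervention than the design supports. The interaction itself is a sensible choice, because the arms are defined by geography and may differ at baseline. What is in question is the power statement attached to it.

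**Working it through.** **Inputs.** From the sample-size section: two-sided alpha 0.05, n = 160 and 112, control prevalence 0.20, odds ratio (OR) 0.50, Rho 0.2 (range 0.2–0.4). From Study Design: visits at baseline and 6, 12 and 18 months. The OR gives intervention odds of 0.25 × 0.5 = 0.125, so p = 0.111. Write v = p(1 − p): 0.16 for control and 0.0988 for intervention.

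**Step 1: reproduce the 83%.** The mean of three visits has variance factor f = (1 + 2 × 0.2)/3 = 0.467.
- Proportion scale: SE = √[0.467 × (0.16/112 + 0.0988/160)] = 0.0309; z = 0.0889/0.0309 = 2.88; power = Φ(2.88 − 1.96) = 82%.
- Log-odds scale: SE = √[0.467 × (1/(112 × 0.16) + 1/(160 × 0.0988))] = 0.236; z = 0.693/0.236 = 2.94; power = 84%.

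The pooled-variance version also gives 84%. With one visit the result is 50–53%, with two 72–74% and with four 87–89%. The stated figure therefore fits the average of the three follow-up visits, without baseline.

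**Step 2: mean follow-up versus baseline, by arm.** Assume 20% prevalence at baseline in both arms, v₀ = 0.16. On the log-odds scale:
- Control variance: (1/(112 × 0.16)) × (1 + f − 2Rho) = 0.0558 × 1.067 = 0.0595.
- Intervention variance: (1/160) × [1/v₀ + f/v₁ − 2Rho/√(v₀v₁)] = (6.25 + 4.73 − 3.18)/160 = 0.0487.
- SE = √0.1082 = 0.329; z = 0.693/0.329 = 2.11; power = 56%.

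At Rho 0.4, f = 0.6, the variances are 0.0446 and 0.0373, SE = 0.286, z = 2.42 and power is 68%.

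**Step 3: other forms of the interaction.** These use the information matrix Σ n D′V⁻¹D, with logit link, exchangeable correlation and complete visits. For a linear trend reaching OR 0.50 at month 18, the SE of the 18-month difference in change is 0.391, so z = 0.693/0.391 = 1.77 and power is 43%.

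| Interaction tested, and true effect | Rho 0.2 | Rho 0.4 |
|---|---|---|
| Mean follow-up vs baseline; OR 0.50 at every follow-up | 56% | 68% |
| Linear slope; OR 0.50 at month 18 | 43% | 53% |
| Linear slope; OR 0.50 at every follow-up | 40% | 50% |
| Linear slope; OR 0.50 at month 12 (about 0.35 at month 18) | 73% | 83% |
| *Averaged follow-up comparison (Step 1), for reference* | 82–84% | 72–74% |

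Higher Rho helps the interaction and hurts the averaged comparison.

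**Step 4: dependence on the endpoint.** Baseline condomless sex with clients was 45.2% (Cohort Participant Characteristics). There v₀ = 0.248, p₁ = 0.292 and v₁ = 0.207. Step 2 then gives SE = √(0.0384 + 0.0283) = 0.258, z = 2.68 and power 77% at Rho 0.2; at Rho 0.4 it is 87% (both at 160/112).

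**Step 5: achieved sample.** The article does not give visit-level attendance by arm. Assume 224/161 at baseline and each follow-up visit attended independently with probability 0.65. Mean follow-up versus baseline (OR 0.50 at every follow-up) then has the following power over Rho 0.2–0.4:
- 64–75% at 20% prevalence
- 84–92% at 45.2% (condomless sex)
- 56–67% at 86.8% (cocaine use)

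**The case against.** Several points on the other side stand.

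- **The sum is right.** The 83% is correct for the contrast that it used, so a reader should not call it an arithmetic error.
- **Rho 0.2 is not a flattering choice for the named test.** It is the favourable end of the plan's range only for the averaged comparison. For the interaction it is the unfavourable end.
- **The retention shortfall is disclosed.** Multiplying 224/161 by 0.65 gives about 146/105, below the assumed 160/112. But that treats retention as complete-case. Cohort Retention Methods keeps women who miss a visit, and the mixed model uses every observed visit. With all visits used, mean follow-up versus baseline has about 64–75% at 20% prevalence (Step 5), more than the 56–68% at 160/112.
- **20% is an example.** The assumptions allow for varying levels of baseline risk behaviour.
- **The article leaves the coding of time and the timing of the OR open.** It says that full power details are available on request. Reaching 83% in Step 3 takes both the 12-month reading and Rho 0.4, whereas the plan states 83% at Rho 0.2. An OR of 0.50 per visit would give about 99%, but implies 0.125 at month 18, which the text does not say. Forcing equal baselines in the model gives about 87%, but the plan's model has an arm term and the trial is nonrandomized.

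A reader might infer that the behavioural analysis is little better than a coin toss, or that it could not have shown an OR of 0.50. The documents do not support either: even 56% power is a fair chance of detection, and the condom-use endpoint is considerably better placed.

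**Conclusion.** The point holds as a mismatch between calculation and analysis. The article prints a power figure and names an effect test, and the two do not correspond. At the stated inputs, the interaction has about 56% power (mean follow-up versus baseline) or 43% (linear trend reaching 0.50 at month 18), against 83% stated. These become 68% and 53% at Rho 0.4, and 73% at Rho 0.2 if 0.50 is the 12-month value of a linear trend. At 45.2% prevalence, follow-up versus baseline has 77–87%.

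The figures assume equal baselines, an exchangeable correlation and a population-averaged OR of 0.50. If 0.50 is instead the subject-specific OR of the random-effects model, power is lower: a small simulation (150 runs, standard error about 4 points) gave 41% for follow-up versus baseline at Rho 0.2. Clustering in the ten recruitment areas is ignored throughout; differences between areas in change over time would lower the interaction's power further.

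All women have passed their 18-month window, so the sample cannot change. The correction matters for how a null result is read and for fixing the contrast in advance.

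**What to change.** 1. Restate the power, or the OR detectable at 80%, for the interaction test. Use the achieved sample (224/161 at baseline, about 65% retained, all observed visits used), Rho from 0.2 to 0.4, and the observed baseline prevalence of each primary behavioural endpoint. State the time at which the OR applies.
2. Before outcome analysis, fix one primary interaction contrast that matches the restated power. One option is categorical visit, with the mean of the three arm-by-visit interactions (6, 12 and 18 months) against baseline. At 160/112, 20% prevalence and Rho 0.2, this has about 56% power under a sustained effect, where a single linear slope has about 40%.

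**Cost.** The stated power becomes less favourable. The mean contrast is also less sensitive to a steadily growing effect. If the OR reaches 0.50 only at month 18, the mean log OR over follow-up is two thirds of 0.693, or 0.462. With an SE of about 0.324 this gives z = 1.42 and about 30% power, against 43% for the slope. The choice should therefore follow the expected course of the effect. No new data are needed.

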For the primary biological endpoint of HIV and STI incidence, we will initially estimate cumulative incidence rates in both the intervention and comparison participants as a binary outcome and construct confidence intervals, accounting for the correlation structure because of nesting in geographic recruitment areas. The intervention’s effect will be assessed using an unadjusted random effect logistic model, with the intervention indicator as the only explanatory variable. The model will be expanded to include baseline covariates, such as demographic characteristics, history of sex work, and baseline risk behaviors (ie, condom use). A more detailed analysis will employ person-time methods with Poisson regression models to allow for time-updated covariates measured over time. Those lost to follow-up will contribute time-at-risk until the time of their last visit.

Finally, to evaluate the reach of the intervention, we will estimate SPARC involvement of FSWs in the independent cross-sectional survey at the 18-month follow-up period. We will also compare this sample with the FSW cohort at 18 months to assess their comparability or differences regarding demographic and risk profiles using logistic regression with group membership as the outcome variable.

To address aim 2, we will first describe changes over time in various sociostructural (ie, social cohesion and stigma) and structural vulnerability (eg, housing stability) indicators. We will then contrast these trends between the intervention and comparison groups. Social cohesion, social participation, and collective action will be analyzed as aggregate measures, the form of which will be determined by exploratory analysis. Specific models for formal statistical comparisons will be developed based on exploratory analysis, identifying both the distributional properties of the indicators and the shape of changes over time. To assess the association of these changes with the study’s primary endpoints, we will develop random effects logistic models, where the changes in structural indicators at each visit compared with baseline will be the main explanatory factors, in addition to the intervention indicator. The random effects will reflect the nesting of observations within the recruitment area and person over time.

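### Neither stated power allows for correlation within the 10 recruitment areas that define the arms, so both are overstated if any such correlation exists

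*Protocol article*

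**What the plan says.** All from the protocol article.

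- **Cohort Study Target Population and Sample.** A woman's arm is fixed by where she was recruited. Five sizing assumptions are listed. The only correlation among them is the one within a woman: "intraperson correlation (Rho)=0.2-0.4, (4) varying levels of baseline risk behavior rate". The test level is "a 2-sided α=.05". The behavioral calculation takes 160 and 112 women after dropout, at Rho 0.2, and its result reads "the power is 83% to detect an odds ratio of 0.50, assuming a 20% prevalence rate of a risk behavior". For incidence, with 170 and 120 women and 6% a year, power is put at 80% for a rate ratio of 0.28.
- **Cohort Recruitment.** The sampling frame has 10 small areas. "Among them, 6 were located in the intervention area and 4 in the control area".
- **Statistical Analysis.** The main models carry "variance components that reflect the potential correlations among FSWs recruited from the same area". The incidence estimates are to be made "accounting for the correlation structure because of nesting in geographic recruitment areas".

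**The concern.** Area is the unit that determines arm, and there are only 10 areas. When women from the same area resemble each other, the arm comparison carries between-area variation that more women per area cannot remove. The analysis plan recognises this and the sizing does not. With roughly 27 to 30 women per area, even a very small area correlation matters.

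Recruitment has closed, so what is at stake is interpretation. A null result would be read against 83% and 80%, figures that do not belong to an area-allocated design.

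**Working it through.** **Inputs from the article.** Two-sided alpha 0.05; 160 and 112 women; control prevalence 20%; odds ratio 0.50; three follow-up visits; Rho 0.2 to 0.4. For incidence: 170 and 120 women, 6% a year, rate ratio 0.28, 18 months (Cohort Retention Methods). Areas: 6 and 4.

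**Assumed, not in the article.** Area ICC of 0.005 to 0.02; women spread evenly over areas; an area effect that persists across visits.

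**1. Reproduce the 83%.** Control odds are 0.20/0.80 = 0.25. Halved, they give 0.125, so the intervention prevalence is 0.125/1.125 = 0.111 and the difference is 0.0889. The mean of three visits has variance factor (1 + 2 × 0.2)/3 = 0.467.

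- Unpooled SE = √(0.467 × [0.2 × 0.8/112 + 0.111 × 0.889/160]) = 0.0309. Then 0.0889/0.0309 − 1.96 = 0.92, which is power 82.0%.
- With the pooled null SE (mean prevalence 0.148, SE 0.0299): (0.0889 − 1.96 × 0.0299)/0.0309 = 0.98, which is power 83.7%.

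The printed 83% lies between these two, with no area term.

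**2. Add an area term to the behavioral comparison of follow-up levels.** Women per area: 112/4 = 28 and 160/6 = 26.7. The variance factor per woman becomes (1 + 2 × Rho)/3 + (m − 1) × ICC. At Rho 0.2 and ICC 0.01 it is 0.737 and 0.723, about 1.56 times 0.467. At ICC 0.02 it is 1.007 and 0.980, about 2.1 times.

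| Area ICC | Power, Rho 0.2 | Power, Rho 0.4 |
|---|---|---|
| 0 | 82-84% | 72-74% |
| 0.005 | 72-74% | 63-66% |
| 0.01 | 63-66% | 56-59% |
| 0.02 | 50-53% | 46-48% |

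Each range runs from unpooled to pooled. At Rho 0.2 with the pooled form, an ICC of about 0.002 already brings power to 80%, and about 0.023 brings it to 50%. A t reference on 10 − 2 = 8 df lowers power further: 71% at ICC 0 and 52% at ICC 0.01 (unpooled, Rho 0.2). If area correlation instead faded between visits in proportion to Rho, the factor would be 0.467 × [1 + (m − 1) × ICC], and the pooled powers would be 75% at 0.01 and 67% at 0.02.

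**3. Incidence.** Over 18 months, 6% a year gives 0.09 in control and 0.28 × 0.09 = 0.0252 in intervention, or 10.8 and 4.28 expected events. There is one binary outcome per woman and no correlation term.

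- Log rate ratio Wald: 1.273/√(1/10.8 + 1/4.28) − 1.96 = 0.27, which is 61%.
- Pooled two-proportion: (0.0648 − 1.96 × 0.0265)/0.0288 = 0.45, which is 67%.

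Women per area: 120/4 = 30 and 170/6 = 28.3. The factor is 1 + (m − 1) × ICC: 1.29 and 1.27 at ICC 0.01, 1.58 and 1.55 at 0.02.

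| Area ICC | Wald | Pooled |
|---|---|---|
| 0 | 61% | 67% |
| 0.01 | 50.5% | 57% |
| 0.02 | 43% | 50% |

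The loss is about 10 points at 0.01 and 17-18 at 0.02. The printed 80% is not reached at 18 months even without clustering. The pooled form gives 79.6% over 24 months (12% versus 3.36%), again with no area term. That gap is a separate matter.

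**The case against.** **The planned behavioral test is not a comparison of follow-up levels.** The Statistical Analysis section assesses the effect through the arm-by-time interaction, where a stable area effect largely cancels and only area-by-time variation remains. This stands. The behavioral table shows what happens to the calculation behind the 83%; it does not give the power of the planned test. A simple change-from-baseline contrast with no area term gives about 48-50% at Rho 0.2 and 59-62% at Rho 0.4. So Rho 0.2 is the favorable end only for the level comparison, and its choice is not a fault in itself.

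**No area ICC is given.** This also stands. A reader might infer that true power is about 50-65%. The article does not support that: 0.005 to 0.02 is an assumption, and covariate adjustment could lower any residual correlation.

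**An article condenses, and full power details are offered on request.** This would answer a complaint about missing detail. It does not rescue the 83%, because the printed inputs already produce it with zero area correlation.

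**The figures belong to the initial target of 350, and power was later reassessed at about 65% retention.** True, but the reassessed power is not printed, so these are the only powers a reader has.

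**The analysis already carries area terms.** Also true. A reader might infer that the analysis ignores clustering; it does not. The fault is confined to the sizing statement.

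**Conclusion.** The point holds. Neither printed power includes area-level correlation, although area determines arm and the analyses are to account for it. For any positive area correlation, the level comparison that reproduces the 83% and the single-outcome incidence comparison both have less power than they would without it. For the planned arm-by-time test, the loss comes through area-by-time variation.

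The direction is certain; the size is conditional on the assumed ICC range, even allocation of women across areas and, for behavior, an area effect that persists across visits. It would be wrong to attribute the whole distance between 80% and the 18-month incidence figures to clustering: 13 to 19 points of it (80 − 67 and 80 − 61) are present before any area term enters. Nor does the finding call for more women. It concerns what the stated powers can be taken to mean.

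**What to change.** In the sample size section, restate both powers for 6 versus 4 areas as a small table over a stated range of area correlation (for example 0.005 to 0.02), with Rho across its full 0.2 to 0.4 for the behavioral endpoint.

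- **Behavioral endpoint:** base the power on the planned arm-by-time contrast, with an assumed area-by-time component. Baseline data alone cannot supply that component.
- **Incidence:** use an area ICC. The baseline gonorrhea and chlamydia results can guide it, but an estimate from 10 areas will be rough and imprecise.
- **Both:** state whether a small-sample reference for 10 areas is used.

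If no restatement is made, say plainly that the 83% and 80% ignore area clustering and do not describe this design.

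The cost is a recalculation, one paragraph and a less favorable stated power. No extra enrolment is needed, and the planned models need not change.
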